### Study setting

This clinical trial will be conducted in the Huadong Hospital Affiliated to Fudan University and the Ruijin Hospital Shanghai Jiao Tong University School of Medicine, which are tertiary referral centers in Shanghai, China.

### Study group

This study will consist of two arms, the low-pressure pneumoperitoneum group (LP) and the standard-pressure pneumoperitoneum group (SP). The estimated number of patients hospitalized for prolonged robot-assisted urological surgery is 140 in each group. The IAP for the LP group will be held at 7–10 mmHg, while it will be held at 12–16 mmHg for the SP group, both insufflated at low speed (2 L/min), during the robot-assisted urological surgery. The CO_2_ pneumoperitoneum will be administrated using automatic insufflators (Karl Storz, Tuttlingen, Germany).

### Study time

This will be from 1 January 2016 to 31 December 2017.

### Interventions

Clinical monitoring throughout the surgery, including electrocardiography, arterial oxygen saturation/end-tidal carbon dioxide (SpO_2_/ETCO_2_) and invasive measurements of blood pressure will be exerted on all the subjects involved. All subjects will be premedicated with midazolam 2–4 mg administered intravenously after peripheral intravenous (IV) access has been established, following which a central venous catheter will cannulate the right jugular vein. General anesthetic induction will be performed with lidocaine (1 mg/kg), sufentanil (0.3 μg/kg), propofol (4 μg/mL, plasma concentration regulated by targeted controlled infusion (TCI)) and rocuronium (0.6 mg/kg) administered intravenously in sequence. Endotracheal intubation will be performed after muscle relaxation is adequate (TOF is 0). Two to three percent (1.0–1.5 MAC) sevoflurane in a 50:50 (v/v) oxygen-air mixture (1 L/min) and remifentanil (0.1–0.3 μg/kg/min) will be used for anesthetic maintenance until the end of surgery. To achieve adequate analgesia, sufentanil (0.15 μg/kg) will be administered additionally at the time of incision and suture, respectively. To maintain appropriate neuromuscular block, cisatracurium is continuously infused at a rate of 1–2 μg/kg/min until 20 min before surgery completion. Depth of anesthesia is monitored with Narcotrend (MonitorTechnik, Bad Bramstedt, Germany) and the ideal value is 37–64.

MAP within ±30 % of baseline is maintained by using phenylephrine or ephedrine when necessary. Colloids (Voluven, or succinylated gelatin for patients with renal dysfunction) and Ringer’s solution are continuously infused at a ratio of 1:3 to replace fluid losses (from blood loss, urine, respiration and perspiration). When it is imperative, blood products are transfused to maintain physiological balance.

The patients will be mechanically ventilated using volume-controlled ventilation mode and a protective lung ventilation strategy. To maintain an ETCO_2_ level within 35–55 mmHg, the tidal volume or the respiratory rate will be adjusted appropriately.

Patients will be extubated in the Postanesthesia Care Unit (PACU). This action allows the depth of anesthesia to be maintained at a constant level until the last measurement is completed. A patient-controlled intravenous analgesia (PCIA) pump with a concentration of 1.5 mg/mL flurbiprofen axetil injection will be used for all patients postoperatively.

During the surgery, a Trendelenburg position of 30° will be applied to all the subjects involved. The position will be adjusted by using the in-built Compass app for the iPhone 6S (Additional file 1: Figure S1. Apple Inc., Cupertino, CA, USA) that is placed on the table.

Hemodynamic indexes, including heart rate, MAP, central venous pressure (CVP), stroke volume (SV), stroke volume variation (SVV) and cardiac output will be measured using the FloTrac system (Edwards Lifesciences LLC, Irvine, CA, USA).

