### Secondary endpoints

Nt-proBNP levels will be measured and recorded at the same time points as for TnT, by the Cobas e 411 analyzer (Roche Diagnostics, Co., Ltd., Mannheim, Germany). Hemodynamic indexes, including heart rate, MAP, CVP, stroke volume (SV), stroke volume variation (SVV) and cardiac output will be measured at the five time points: T1 (5 min after induction), T2 (5 min after CO_2_ pneumoperitoneum is established), T3 (5 min after positioning in the Trendelenburg position), T4 (45 min after Trendelenburg positioning) and T5 (5 min after returning to the horizontal supine position). Respiratory parameters (SpO_2_, ETCO_2_, plateau pressure (PPlat) and tidal volume (Vtide)) will be recorded at all five time points mentioned above.

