### Randomization and blinding

Patients will be recruited in two hospitals: Huadong Hospital Affiliated to Fudan University and Ruijin Hospital Shanghai Jiao Tong University School of Medicine. Patients who meet the eligibility criteria will be randomly assigned to the two treatment groups: SP or LP. The randomization plans will be implemented using statistical software R, and will be stored in an online database. After a clinical evaluation, the surgeon will register the patient using a unique ID assigned to the patient and used to select a random assignment from the database. The physicians will be aware of the group to which the patients are allocated while the patients will not.

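### Tidal volume is a setting that clinicians change to control ETCO2, yet it is listed as a secondary endpoint without respiratory rate; its arm difference, plateau pressure and, to a lesser extent, ETCO2 and MAP cannot be read on their own

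*Protocol article*

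**What the plan says.** Four statements in the protocol article bear on each other.

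- **Interventions, ventilation.** "The patients will be mechanically ventilated using volume-controlled ventilation mode", under a lung-protective strategy for which no volume or pressure limit is given. ETCO2 is to stay within 35–55 mmHg, and for this "the tidal volume or the respiratory rate will be adjusted appropriately".
- **Interventions, circulation.** "MAP within ±30 % of baseline is maintained by using phenylephrine or ephedrine when necessary".
- **Secondary endpoints.** "Respiratory parameters (SpO_2_, ETCO_2_, plateau pressure (PPlat) and tidal volume (Vtide)) will be recorded at all five time points", T1 to T5. MAP is on the haemodynamic list at the same times: "Hemodynamic indexes, including heart rate, MAP, CVP, stroke volume (SV), stroke volume variation (SVV) and cardiac output will be measured". Neither respiratory rate nor vasopressor dose is on either list.
- **Randomization and blinding.** "The physicians will be aware of the group"; patients will not be.

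These are meant as treatment comparisons, not only as monitoring. Sample size calculation claims power of at least 0.85 for differences in certain respiratory parameters, and Statistical analysis plans regression for the effect of the two pressures on pulmonary mechanics. Data collection and management ties data capture to the endpoint lists.

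**The concern.** Under volume control, tidal volume is what the clinician dials in. It responds to the patient only through the clinician, so comparing it between arms compares how clinicians reacted. Respiratory rate, the other lever, is not on the list, so the reaction is only half visible.

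Plateau pressure inherits the problem, because at a given compliance it rises and falls with the volume chosen. ETCO2 is the controlled variable: a larger CO2 load in one arm can be met by more ventilation and leave similar ETCO2 values. MAP is controlled too, but through drugs that raise it.

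The article's own rationale makes this more than theoretical. Background cites more peritoneal CO2 absorption at higher pressure, and Discussion expects lower pulmonary compliance under pneumoperitoneum. If those effects occur, part of them will appear in ventilator settings. A null result on ETCO2 or plateau pressure could then be misread as no effect of pressure, and a tidal-volume difference could be misread as an effect on the lung.

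**Working it through.** **The plan's own figure.** The 0.85 power for respiratory parameters cannot be reproduced, since no effect size, SD or alpha is given. With 140 per arm and an assumed two-sided alpha of 0.05, it corresponds to a standardised difference of (1.960 + 1.036) × √(2/140) = 0.358. This does not decide the point.

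**1. Tidal volume (assumed steady-state model).** Take ETCO2 as proportional to CO2 load ÷ (tidal volume × rate). Let the load ratio between arms be r, fully corrected, with a share s of the correction made through tidal volume. Then the tidal-volume ratio is r^s, the rate ratio is r^(1−s), and the ETCO2 ratio is 1.00. For an assumed r = 1.10:

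| Share through tidal volume | Tidal-volume ratio | ETCO2 ratio | Minute-ventilation ratio |
|---|---|---|---|
| 0 | 1.00 | 1.00 | 1.10 |
| 0.5 | 1.05 | 1.00 | 1.10 |
| 1 | 1.10 | 1.00 | 1.10 |

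Without correction the tidal-volume ratio would be 1.00. Adjustment can therefore create a tidal-volume difference or leave none, while minute ventilation shows the 1.10 in every row. Minute ventilation needs the rate.

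**2. Plateau pressure (assumed compliance 30 mL/cmH2O in the low arm, 25 in the standard arm).** Pressure above PEEP = volume ÷ compliance. The low arm at 500 mL gives 500/30 = 16.7 cmH2O.

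| Standard-arm volume | Pressure above PEEP | Difference from 16.7 | Volume ÷ pressure |
|---|---|---|---|
| 500 mL | 500/25 = 20.0 | 3.3 | 25 |
| 550 mL | 550/25 = 22.0 | 5.3 | 25 |
| 450 mL | 450/25 = 18.0 | 1.3 | 25 |

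The ETCO2 rule, with more CO2 absorbed at higher pressure, points to more volume or more rate in the standard arm. A lung-protective motive could point to less volume. The article fixes neither. The ratio stays at 30 against 25 throughout.

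**3. ETCO2.** Suppose correction only brings values back to the band limits a = 35 and b = 55. For a normal variable with mean μ and SD σ, with α = (a−μ)/σ and β = (b−μ)/σ, the expected value after correction is aΦ(α) + b[1−Φ(β)] + μ[Φ(β)−Φ(α)] − σ[φ(β)−φ(α)]. Example: means 42 and 44, SD 6 become 42.33 and 44.10, so 1.77 of 2 mmHg remains (88%). Over assumed SDs of 4 to 8 and a true difference of 2 mmHg:

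| Assumed arm means | Share of the difference kept |
|---|---|
| 42 vs 44, or 46 vs 48 | 77–97% |
| 38 vs 40, or 50 vs 52 | 67–84% |
| 54 vs 56 | about 50% |

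Power falls less than the difference, because correction also narrows the spread. At SD 6 with 140 per arm it goes from 0.80 to 0.78 for 42 vs 44, and from 0.80 to 0.66 for 54 vs 56.

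**4. MAP.** The named drugs raise pressure, so the written control acts at −30% only. The same formula with no upper limit, for a true difference of 5 points (percent of baseline) and assumed SDs of 10 to 20, keeps 95–100% at means 0 vs 5, practically all at 20 vs 25, 73–89% at −20 vs −15, and 55–60% at −30 vs −25. Background and Discussion expect pneumoperitoneum to raise MAP, which is away from the controlled limit.

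**The case against.** The strongest reply has three parts.

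- **The bands are wide and MAP control is one-sided.** A reader might infer that tidal volume, ETCO2 and MAP are each steered to a target, so that every comparison is biased towards no difference. The article does not support this. Tidal volume has no target of its own and its contrast can move away from zero. ETCO2 and MAP are held in ranges within which differences remain visible. Nothing in the article places an arm mean at a limit. This part stands and limits the claim. One reservation is that the article sets no trigger for adjusting ventilation, so staff may act before a limit is reached, and the ETCO2 shares kept in the calculation may then be too favourable.
- **Much of the remedy is already collected.** Tidal volume and plateau pressure are both recorded at T1–T5, so their ratio can be computed, and T1 values exist for adjustment. This also stands. Recording tidal volume is useful; treating it as an outcome is what misleads.
- **Not listed does not mean not recorded.** Rate and vasopressor dose are probably on the anaesthetic chart, and a fuller protocol or the analysis plan may use them. That is fair, and it makes the change cheap. But the article ties data collection to the endpoint lists, and those lists name one ventilatory lever and not the other. An analysis plan written later cannot use a rate that was not extracted.

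A reader might also infer that volume adjustment would erase most of a plateau-pressure difference. That requires a lower volume in the standard arm, and the only stated reason for changing volume points, if anything, the other way.

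**Conclusion.** The point holds as a problem of interpretation for a few secondary endpoints. Tidal volume is a clinician-set lever; its arm difference has no fixed direction of bias and cannot be read without respiratory rate. Plateau pressure shifts with the chosen volume in either direction. ETCO2 differences may be attenuated, little in mid-band and by about half at a limit. MAP may be attenuated only where vasopressors are given near the lower limit, and is the weakest part.

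The attenuation does not depend on bad faith or on unblinding: blinded control would also pull values together. Knowledge of the arm adds that the timing and choice of adjustment may differ by arm. Nothing here touches the primary endpoint directly, since troponin T has no control rule.

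All sizes rest on assumed loads, compliances, means and SDs, and on correction only at the limits. They show direction and range, not what this trial will see. The change is worth making because it is cheap. No ventilation or blood-pressure limit is judged.

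**What to change.** Leave patient care as it is and change what is extracted and compared.

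1. Keep recording tidal volume, but do not analyse it as an outcome.
2. Make tidal volume divided by plateau pressure the lung-mechanics endpoint, using pressure above PEEP where PEEP is charted. Without subtracting PEEP the ratio still depends somewhat on the volume chosen.
3. Add respiratory rate at T1–T5, and compare minute ventilation (tidal volume × rate) together with ETCO2.
4. Report cumulative phenylephrine and ephedrine dose by arm beside MAP.
5. Adjust each T2–T5 comparison for the T1 value, which precedes insufflation.

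The cost is a few items copied from the anaesthetic chart, a revised endpoint list and slightly more data entry.

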### Primary endpoint

The troponin T level is set as the primary endpoint for this trial to evaluate myocardial injury, and this will be measured for each patient who will undergo prolonged robot-assisted urologic surgery at the following four time points: Ta (2 to 3 h after surgery), Tb (6 h after surgery), Tc (12 h after surgery) and Td (24 h after surgery) using the fifth-generation high-sensitivity TnT assay.

### Secondary endpoints

Nt-proBNP levels will be measured and recorded at the same time points as for TnT, by the Cobas e 411 analyzer (Roche Diagnostics, Co., Ltd., Mannheim, Germany). Hemodynamic indexes, including heart rate, MAP, CVP, stroke volume (SV), stroke volume variation (SVV) and cardiac output will be measured at the five time points: T1 (5 min after induction), T2 (5 min after CO_2_ pneumoperitoneum is established), T3 (5 min after positioning in the Trendelenburg position), T4 (45 min after Trendelenburg positioning) and T5 (5 min after returning to the horizontal supine position). Respiratory parameters (SpO_2_, ETCO_2_, plateau pressure (PPlat) and tidal volume (Vtide)) will be recorded at all five time points mentioned above.

### Sample size calculation

Based on the summary statistics for the troponin T (TnT) values [29, 32], we use a peak TnT level of 0.01 ng/mL or less as the reference group, and to compute the sample sizes. With 140 patients in each of the two treatment groups, the power will be at least 0.70 to detect an increment of 80 % of patients with a TnT level of 0.02 or higher. The total sample size will be 280, which will ensure the detection of differences of certain pre and perioperative respiratory parameter levels (with power of at least 0.85) [33]. The number of enrolled patients in each center is 140, and the allocation ratio for the two groups is 1:1.

### Randomization and blinding

Patients will be recruited in two hospitals: Huadong Hospital Affiliated to Fudan University and Ruijin Hospital Shanghai Jiao Tong University School of Medicine. Patients who meet the eligibility criteria will be randomly assigned to the two treatment groups: SP or LP. The randomization plans will be implemented using statistical software R, and will be stored in an online database. After a clinical evaluation, the surgeon will register the patient using a unique ID assigned to the patient and used to select a random assignment from the database. The physicians will be aware of the group to which the patients are allocated while the patients will not.

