### Study population

Patients who are scheduled to undergo long-duration RALRP or RARC in the Huadong Hospital Affiliated to Fudan University and the Ruijin Hospital Shanghai Jiao Tong University School of Medicine, in line with the inclusion criteria, will be recruited. From the previous data and estimation, the annual number of patients meeting the criteria is over 170.

Inclusion criteria:Scheduled to undergo RALRP or RARC, with an estimated duration of over 3 hAmerican Society of Anesthesiologists’ (ASA) classification of I or IIAge is between 18 and 80 yearsPreoperative troponin T level is normal

Exclusion criteria:Patients with preoperative cardiopulmonary dysfunction who cannot undergo prolonged surgeries in the Trendelenburg position and/or those with severe pulmonary dysfunction with a New York Heart Association (NYHA) classification of III–IVBody Mass Index >30 and weight <18 kgAny intraoperative situation as follows: (1) any cause to cancel the operation or change robot-assisted urological surgery to open surgery, (2) intraoperative cardiovascular accidents

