Other rare complications of pneumoperitoneum include pneumothorax, inadvertent gas embolism, vascular injury and inadvertent extraperitoneal insufflation.

As described above, the pneumoperitoneal physiology in the Trendelenburg position is intricate. We aim to protect the patients from injury by careful preoperative examination, so that undiagnosed conditions can be identified and pretreated. Standard intraoperative monitoring will be used for all patients, and invasive hemodynamic monitoring (Vigileo with the FloTrac system) will be used to monitor the cardiovascular response to pneumoperitoneum and position changes. ETCO_2_ and airway pressure are commonly assessed to assure adequacy of ventilation and blood gas analysis will be conducted when necessary. Other rare complications will be appropriately treated as soon as they are detected.

Data attrition of the clinical trial would affect the validity of our results markedly. In this study, approaches will be adopted to minimize any impact this may bring. The designed follow-up period of this study is only 24 h post surgery, so it is unlikely that the patients who meet the inclusion criteria would drop out, which is confirmed by the ongoing preliminary trial. Besides, we have the capability for a rapid response to any perioperative emergency events. If attrition does occur, we will carefully discuss the reasons and estimate the impact on the trial. If it is not a source of bias we will employ the complete-case method, where the missing data will be excluded from the analysis. As we have a population large enough to complete the trial in the designated period, this is believed to be the simplest and most efficient method for our study.

The main limitation of this trial is the inevitable bias in age and sex distribution of the enrolled patients. Although the age range in the inclusion criteria is set at 18–80 years, most patients requiring urological surgery, especially resection, are middle-aged and elderly men. Thus the conclusion drawn by this study might be not applicable to female patients and cases in different age groups.

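### The surgeon obtains the assignment at registration, so a decision not to proceed before insufflation can be made knowing the arm; releasing the assignment just before insufflation would close that gap

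*Protocol article*

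**What the plan says.** Four parts of the protocol article bear on this.

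- **Randomization and blinding.** Once the patient has been assessed clinically, "the surgeon will register the patient using a unique ID assigned to the patient and used to select a random assignment"; the assignments are held in an online database. On blinding: "The physicians will be aware of the group to which the patients are allocated while the patients will not".
- **Study group.** The two arms are defined by intra-abdominal pressure alone (7–10 against 12–16 mmHg). Insufflation speed is the same in both, and the Interventions section describes one anesthetic regimen for all subjects.
- **Study population.** The exclusion criteria include events described as intraoperative: "any cause to cancel the operation or change robot-assisted urological surgery to open surgery", and "intraoperative cardiovascular accidents".
- **Primary endpoint.** TnT is drawn at "Ta (2 to 3 h after surgery), Tb (6 h after surgery), Tc (12 h after surgery) and Td (24 h after surgery").

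Two further places matter. Secondary endpoints sets the first two hemodynamic readings at "T1 (5 min after induction), T2 (5 min after CO_2_ pneumoperitoneum is established"), so T1 is the only one before insufflation. The Discussion says of attrition: "If it is not a source of bias we will employ the complete-case method, where the missing data will be excluded from the analysis".

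**The concern.** The assignment is available to the person who will operate, apparently well before it is needed. Between registration and insufflation the two arms should be managed identically, yet the team may already know the arm. If a surgeon is uneasy about low pressure in a technically difficult case, or about standard pressure in a frail patient, the decision to go ahead can depend on the arm.

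A randomised patient who is never operated on cannot be recovered by an analysis of everyone as assigned, because each TnT time point is counted from an operation that did not take place. If such losses depend on both arm and risk, the groups compared are no longer the groups randomised. It also means that T1, the one hemodynamic reading before insufflation, follows randomisation when it could precede it.

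**Working it through.** **1. Where patients can be lost, and why**

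| Interval | Event | TnT at the stated times? | Why the patient is lost | Would release just before insufflation help? |
|---|---|---|---|---|
| Assignment to induction | Operation does not go ahead | No, there is no surgery to count from | Outcome undefined; complete-case handling if judged not a source of bias | Yes |
| Induction to insufflation | Operation abandoned | Not as the times are defined | As above, and the exclusion criterion if this counts as intraoperative | Yes |
| After insufflation | Operation stopped, conversion, cardiovascular accident | Obtainable, since there is an operation with an end | The exclusion criterion | No |

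The point concerns the first two rows. A patient who is only rescheduled, and later operated on in the assigned arm, is not lost.

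**2. The plan's own power figure**

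The sample size section gives 140 per arm and power of at least 0.70 for an 80 % increment in patients with TnT of 0.02 or higher. It states no base rate, alpha or sidedness. Assume two-sided alpha 0.05 and a relative increment. Solving for power 0.70 gives a base rate of about 15.1 %, hence 1.8 × 15.1 % = 27.2 %. Take 15.1 % for low pressure (LP) and 27.2 % for standard pressure (SP), following the working hypothesis.

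Power = Φ((d − 1.96·SE0)/SE1), where SE0 uses the pooled proportion and SE1 the separate ones.

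d = 0.121, SE0 = 0.0488, SE1 = 0.0483. (0.121 − 0.0957)/0.0483 ≈ 0.52, and Φ ≈ 0.70.

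So 0.70 is attainable but cannot be confirmed: with the same formula it is 0.49 at a 10 % base rate and 0.85 at 20 %.

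**3. Selective loss, for illustration only**

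Suppose k patients, each with a 60 % risk of TnT of 0.02 or higher, are lost from one arm. Both k and the 60 % are assumptions. The remaining proportion is (140p − 0.6k)/(140 − k), and the formula above is used with 140 − k in the arm that loses patients.

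| Arm losing patients | k | Remaining proportion | Chance of a significant result |
|---|---|---|---|
| none | 0 | LP 0.151, SP 0.272 | 0.70 |
| SP | 5 | SP (38.08 − 3.0)/135 = 0.260 | 0.61 |
| SP | 7 | SP (38.08 − 4.2)/133 = 0.255 | 0.57 |
| LP | 5 | LP (21.14 − 3.0)/135 = 0.134 | 0.81 |
| LP | 7 | LP (21.14 − 4.2)/133 = 0.127 | 0.85 |

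The LP rows do not show better power; the difference has been exaggerated by the loss. With no true effect (15.1 % in both arms), losing 5 or 7 such patients from one arm raises the two-sided type I error from 0.05 to about 0.07 or 0.09.

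**4. Non-selective loss, for comparison**

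Losing 5 % at random from both arms leaves 133 per arm and power 0.68. Loss of numbers alone matters little; dependence on the arm is what matters.

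**The case against.** The strongest objection is that the text does not say what the concern needs. It places registration after a clinical evaluation and gives no time relative to anesthesia, and a condensed article may leave the moment of release to the full protocol. That stands as a limit: the sequence is inferred. But nothing in the text delays release to theatre, and the surgeon is named as the person who obtains the assignment.

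Second, the exclusion criteria refer to intraoperative situations, so they do not literally cover a patient cancelled beforehand. This is correct, but such a patient still has no TnT as defined and drops out through complete-case handling. The Discussion does promise to examine reasons for attrition and restricts complete-case analysis to attrition judged unbiased. That is a partial safeguard, but it cannot supply an outcome for an operation that never happened.

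Third, a reader might infer that only a later release can prevent these losses, or that every cancelled patient lacks TnT. The documents support neither. An operation stopped partway has an end from which TnT can be timed. Conversions, cardiovascular accidents and cancellations after insufflation are lost because the exclusion criteria remove them, and later release does nothing for them. Those events are also the ones most plausibly linked to pressure or to TnT.

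Fourth, a reader might infer that knowledge of the arm shifts T1. The documents do not support that: induction follows one regimen for all subjects, and T1 is nowhere called a baseline or used as a covariate.

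Finally, the article admits only ASA I–II patients with normal preoperative troponin, so nothing in it supports a subgroup at 60 % risk. This stands; the figures are an illustration only.

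**Conclusion.** The point holds in a limited form. The plan lets the operating surgeon obtain the assignment earlier than the design requires, with physicians aware of the arm, so a decision not to proceed before insufflation can depend on it. For a patient never operated on, the primary endpoint does not exist.

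Its size is unknown. The documents give no cancellation rate, do not say who decides to cancel, and give no risk profile for such patients. The illustration runs from 0.57 to 0.85 around a planned 0.70 according to which arm loses patients, so neither direction nor magnitude is established. It also rests on an assumed two-sided alpha of 0.05, a back-solved base rate, and an assumed number and risk of lost patients.

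The change is still worth making: the gap is avoidable, the arms do not differ before insufflation, and the online database already exists.

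**What to change.** Keep screening, consent and registration as they are. Release the assignment from the existing online database in theatre, after induction and the T1 reading and immediately before insufflation. Have it requested by someone already present other than the operating surgeon, and count a patient as randomised only at that release. Cancellations before insufflation then cannot depend on the arm and become pre-randomisation losses, and T1 precedes randomisation. If the full protocol already works this way, one sentence stating it is enough.

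Separately, and still needed: remove the intraoperative events (cancellation after insufflation, conversion, cardiovascular accident) as grounds for exclusion, analyse those patients in their assigned arm, and report such events by arm.

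The cost is access to the database from theatre, which both centers would need to confirm. The small downside is that the pressure cannot be planned in advance. The article's Trial status section says enrollment had not started, so the change was feasible when it was written.
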